### Statistical analysis plan

#### Sample size and power calculation

The estimated proportion of diabetic patients 1 year after transplantation is 40% in group 2 (P_2_) and the expected decrease in group 1 (P_1_) is 50% (i.e., 20% at 1 year) [4, 5]. The expected 50% decrease is estimated according to the results obtained with the insulin treatment of Hecking et al. (100% decrease at 1 year) [6]. With the hypotheses H0 (P_2_ − P_1_ = 0; null hypothesis) and H1 (P_2_ − P_1_ ≠ 0; altenative hypothesis) and by considering a group sequential design with a Z score test (pooled estimate for variance estimation), a bilateral alpha risk of 5% and a ß risk of 20%, it will be necessary to randomize 84 patients per group (a total of 168 patients). We expect 10% of patients at 1 year to be non-evaluable and thus we will include 186 patients in total. An interim analysis is planned by the statistician of the investigation team (without the investor being aware of the lifting of the blind) to reject H0 or H1 when at least 84 patients are randomized with one year of follow-up (42 in each group; 50% of the information fraction) using alpha spending function and O’Brien Fleming boundaries. Sample size calculations were performed with the EAST 6 software.

Moreover, as supportive analysis with this sample size will be able to demonstrate an improvement in the time of diabetes-free occurrence from 40% to 20% (hazard ratio of 0.43) with a bilateral alpha risk of 5% and we will have 90% statistical power with 63 events.

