
### Justification of the primary outcome

The primary endpoint is the proportion of diabetic patients 1 year after transplantation, defined as patients receiving a diabetic treatment, patients with a fasting glucose above 7 mmol/l, and/or patients with an abnormal OGTT. Unlike the Hecking et al. [6] study, we chose de novo diabetes, a clinically relevant criterion, as the main criterion and not a surrogate marker. This will actually determine if this preventative treatment effectively protects from the disease. Consequently, the results will be expressed as the number of patients with diabetes, as defined previously, at a given time. At transplant, 100% of patients will be considered as diabetic because all patients will be treated, at least, with vildagliptin (or placebo) for two months. At 2 months, treatment with vildagliptin, prescribed in the context of the study, will be stopped and only some patients will be considered diabetic (abnormal dosages and/or prescription of a new antidiabetic treatment) at 3 months. This number of patients may still vary at 6 months and one year post-transplant [6]. The main criterion is the number of patients with diabetes at one year.

The onset of diabetes at other times (3 and 6 months) as well as abnormal glucose indicators (fasting glucose, OGTT, glycated hemoglobin) at each time will be assessed as secondary endpoints. These data will also be correlated with the clinical events (occurrence of acute rejection, infection, graft loss, and patient death at 3, 6, and 12 months after transplantation), the medical history, and the biological assessment of the patients.

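### The supportive time-to-diabetes analysis is credited with 63 events and 90% power, but the plan's own one-year rates give about 50 to 56 events and roughly 84 to 87% power

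*Protocol article*

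**What the plan says.** All design figures are in the protocol article, section Sample size and power calculation. For the primary comparison: "The estimated proportion of diabetic patients 1 year after transplantation is 40% in group 2", with a halving to 20% expected under vildagliptin. From this, "it will be necessary to randomize 84 patients per group (a total of 168 patients"). The allowance for loss is stated next: "We expect 10% of patients at 1 year to be non-evaluable and thus we will include 186 patients in total".

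The next paragraph turns to time to diabetes. It says that "as supportive analysis with this sample size will be able to demonstrate an improvement", described as an "improvement in the time of diabetes-free occurrence from 40% to 20% (hazard ratio of 0.43"). The test is two-sided at 5%, and the power claim reads: "we will have 90% statistical power with 63 events".

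Two other places bear on this. Study visits lists M12 as the last of five visits, and the health economics section also treats M12 as the last visit. Justification of the primary outcome says: "At transplant, 100% of patients will be considered as diabetic because all patients will be treated" with study drug or placebo for two months. It adds that only some patients will count as diabetic at 3 months and that the number may still change by 6 and 12 months.

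**The concern.** A time-to-event power statement needs two things: the number of events required for the stated power, and a sample and follow-up that will produce them. The article presents 63 events as what this sample size provides, but gives one-year rates, a sample size and a last visit from which the expected count can be worked out, and that count is lower. A reader would credit the supportive analysis with more power than the plan's inputs support, and could over-interpret a non-significant result from it.

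The sentence on diabetic status at transplant raises a smaller question of wording. A time-to-onset analysis starts from patients who are free of the event, and patients with a history of diabetes are excluded. A statement that everyone is diabetic at transplant, placebo patients included, does not fit with either.

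**Working it through.** **Inputs (protocol article).** One-year proportions 40% (placebo) and 20% (vildagliptin); 84 per group, 168 in total; 186 included (93 per group), allowing for 10% non-evaluable; two-sided 5%; hazard ratio 0.43; 63 events; 90% power: all from Sample size and power calculation. Allocation 1:1: Randomization. Last visit M12: Study visits.

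**Step 1. Reproduce the hazard ratio.** With proportional hazards, HR = ln(1 − 0.20)/ln(1 − 0.40) = ln 0.8/ln 0.6 = 0.4368. The printed 0.43 is this value cut to two decimals.

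**Step 2. Reproduce the event requirement.** Schoenfeld, 1:1: d = 4(1.960 + 1.282)²/(ln HR)².
- HR 0.4368: 61.3, so 62 events
- HR 0.44: 63 events
- HR 0.43: 59.0, so 60 events

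Conversely, power = Φ(√d/2 × |ln HR| − 1.960). With d = 63 and HR 0.4368 this is 90.8%. The link between 63 events and 90% power is therefore reproduced.

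**Step 3. Expected events by M12,** taking events as equal to the one-year proportions:
- 168 evaluable: 84 × (0.40 + 0.20) = 50.4
- 186 with no loss: 93 × 0.60 = 55.8
- 186 with 10% lost over the year at a constant rate: about 53

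The shortfall against 63 is 12.6 events at 168 patients and 7.2 at 186. The average rate is 30%, so 63 events need 63/0.30 = 210 patients. At constant hazards, 63 events would accrue after about 16 months in 168 patients or 14 months in 186. Both are later than M12.

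**Step 4. Power at those counts.** The Freedman version is Φ(√d × (1 − HR)/(1 + HR) − 1.960).

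| Events | HR | Schoenfeld | Freedman |
|---|---|---|---|
| 50.4 | 0.4368 | 83.6% | 79.5% |
| 50.4 | 0.43 | 85.0% | 80.8% |
| 55.8 | 0.4368 | 87.2% | 83.4% |
| 55.8 | 0.43 | 88.3% | 84.6% |
| 63 | 0.4368 | 90.8% | 87.5% |

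A log-rank simulation (exponential times, 12 months of follow-up, 20,000 runs) gave 82% for 84 per arm, 84% for 93 per arm with 10% loss, and 86% for 93 per arm without loss. None of these reaches 90%.

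**Step 5. Primary sample size.** The fixed-design pooled Z formula for 40% against 20% at 80% power gives 82 per arm. The stated 84 is consistent with that plus a small allowance for the group sequential design, so the error does not reach the primary calculation.

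**The case against.** The strongest counter-argument is that 40% and 20% are proportions diabetic at one year, whereas a time-to-first-diabetes analysis counts everyone who becomes diabetic at any time. That number cannot be lower, and it could be higher: the Background says most cases arise in the first months, and the primary outcome section expects the number of diabetic patients to vary. Among 186 patients, 63 events would need a cumulative incidence of 63/186 = 33.9% rather than 30%, about 7 cases that remit before M12. This stands as a condition on the shortfall. It does not restore the 90%, because the article gives no remission rate and ties its hazard ratio to the same 40% and 20%. If transient cases are counted, neither the rates nor the hazard ratio applies as stated.

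It can also be said that the sentence means only that power would be 90% if 63 events occurred. That conditional statement is correct, but the article attaches it to this sample size and describes no follow-up beyond M12.

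Finally, the analysis is supportive. The interim boundaries, the final decision rule and the number of patients all rest on the comparison of proportions. This stands, and it limits the seriousness of the point.

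A reader might infer more than the documents support on two counts. First, that the survival analysis is undefined because nobody is at risk at transplant. The sentence on diabetic status describes how many patients count as diabetic at a given time; it does not define the event or origin of the survival analysis. Study drug stops at 2 months, and from month 3 the same section rests diabetic status on abnormal results or a new antidiabetic prescription, so status from M3 to M12 is not distorted. Second, that a hazard ratio of 0.43 instead of 0.44 is an error of substance. It is truncation, and using 0.43 throughout still leaves power at 85.0 to 88.3% by Schoenfeld.

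**Conclusion.** The point holds as a minor correction. The requirement of about 63 events for 90% power is right at a hazard ratio of about 0.437 to 0.44. The claim that this sample size provides it is not: the plan's own rates and follow-up give about 50 events in 168 patients and at most about 56 in 186, a shortfall of 7 to 13 events (11 to 20% of 63). Power is about 84%, at most 87%, by Schoenfeld at HR 0.437, and about 79 to 86% by Freedman or simulation.

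This rests on proportional hazards, on follow-up ending at M12, and on events being equal to the one-year proportions; uncounted transient cases would raise the count by an amount the article does not give. The primary sample size, the interim analysis and the final test are unaffected.

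The sentence that treats all patients as diabetic at transplant is a separate wording inconsistency. It does not make the time-to-diabetes analysis impossible.

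**What to change.** Replace the supportive power sentence with wording such as: *about 50 events are expected among 168 evaluable patients (at most 56 among 186), giving about 84% (at most 87%) power by the Schoenfeld formula for a hazard ratio of 0.44 at a two-sided 5% level*. Add that the Freedman formula or simulation gives somewhat lower values (about 79 to 86%), and that the count takes events as equal to the one-year proportions. If transient diabetes is meant to count as an event, state the cumulative incidence assumed in each arm and derive the hazard ratio and power from that.

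Separately, reconcile the sentence on diabetic status at transplant with the time-to-diabetes analysis and with the exclusion of a history of diabetes, by stating that blinded study vildagliptin or placebo does not itself count as a diabetic treatment for the endpoints. A rule that onset counts only from M3 is not needed for this; it would be a new design choice.

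The cost is wording and a slightly less favourable stated power. No extra patients, visits or follow-up are needed. The change is best made before the database is frozen, when the analysis plan is due to be approved.

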### Statistical analysis

The statistical analysis plan (final and HRQoL analyses) will be written and approved before the database is frozen.

#### Primary outcome analysis

The intention to treat (ITT) population will be used for efficacy parameter analysis (all randomized patients whatever the eligibility criteria and treatment received).

A Z score test with pooled estimate for variance estimation will be used to compare the estimated proportion of diabetic patients 1 year after transplantation between the two arms. A Lan-DeMets alpha spending function with O’Brien and Fleming boundaries (function depending on the information fraction in the ITT population) will be used. For the interim analysis with 84 informative patients at 1 year of follow-up (50% of the information fraction) we will reject H0 (efficacy) or reject H1 (futility) if the test p value is lower than or equal to 0.0003 and higher than 0.715, respectively. If the p value is higher than 0.0003 but lower than or equal to 0.715, we can’t make a conclusion and the study will continue. At the end of the study with 168 informative patients at 1 year of follow-up, we will reject H0 and then accept H1only if the test p value is lower than or equal to 0.049.

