## Methods/design

### Study design

This is a multicenter, double-blind, placebo-controlled randomized clinical trial. The study will include 186 patients receiving a kidney transplant and matching the criteria for inclusion. Recruitment will be done in ten French transplant units: Amiens, Besançon, Brest, Lille, Nice, Paris (Necker and Tenon), Rennes, Poitiers, and Tours. Patients will be randomized into two groups: group 1 will be treated with vildagliptin and group 2 will be treated with placebo. The treatment duration will be 2 months. The dose will be adjusted during treatment, depending on the results of glomerular filtration rate. The administration of vildagliptin begins before entering the operating theatre. Blood glucose is controlled and if necessary hyperglycemia will be treated according to current recommendations, regardless of the group and the study.

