#### Randomization

Patients will be randomized 1:1 into two groups using a minimization technique with stratification according to center and the number of risk factors for developing diabetes (two or three).Group 1 (interventional group) will be treated with vildagliptin 100 or 50 mg/day for 2 months (depending on whether their glomerular filtration rate is above or below 50 ml/min; Modification of Diet in Renal Disease (MDRD) equation).Group 2 (placebo group) will be treated with placebo according to the same dosage.

Random allocation sequence is generated using CleanWeb™. The minimization algorithm takes into account already randomized patients in order to allocate a new treatment to minimize difference between stratification criteria. The randomization result provided by the system is attributed in 80% of cases; otherwise, the other treatment is attributed. Neither the nurse nor the doctor nor the patient will know the nature of the ingested tablets. The blinding is created by the clinical research associate coordinator. The randomization number is assigned directly to the centers via CleanWeb™.

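### Allocation is balanced on centre and number of risk factors but the primary Z test ignores both; to the extent they predict diabetes, the test is mildly conservative and some power is forgone

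*Protocol article*

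**What the plan says.** Under Randomization, patients are allocated 1:1 "using a minimization technique with stratification according to center and the number of risk factors for developing diabetes (two or three". The algorithm has a random element: "The randomization result provided by the system is attributed in 80% of cases", and the other arm is given in the remainder. The Study design section gives ten centres.

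Under Primary outcome analysis the test, its variance estimator and its p-value limits are all fixed: "A Z score test with pooled estimate for variance estimation will be used to compare the estimated proportion of diabetic patients". No stratum or covariate is named. Sample size and power calculation uses the same test: "it will be necessary to randomize 84 patients per group (a total of 168 patients".

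The only models described for diabetes occurrence are under Secondary outcome, exploratory, and sensitivity analyses. They are logistic models that look for prognostic factors, admit covariates on a univariate p value of at most 0.1, and do not force in the balancing factors.

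**The concern.** Minimisation keeps the arms alike on its factors. If those factors predict the outcome, the arm difference varies less over repeated trials than it would under simple randomisation. The pooled variance p(1−p)(1/n1 + 1/n0) takes no account of this: it still counts the variation due to the factors. The Z statistic then has variance below 1 under the null, and the boundaries are applied at less than their nominal level.

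The protocol gives reason to expect some prognostic value. The Inclusion criteria define high risk by these factors, and Conditions for patient selection in the Discussion keeps them because they discriminate. What is at stake is precision that the allocation scheme has already provided and the analysis does not use.

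**Working it through.** **1. The plan's own figure.** Inputs from Sample size and power calculation: 40% versus 20%, two-sided 5%, power 80%, pooled variance, mean rate 0.30.

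n = [1.960·√(2·0.30·0.70) + 0.8416·√(0.40·0.60 + 0.20·0.80)]² / 0.20² = [1.960·0.6481 + 0.8416·0.6325]² / 0.04 = 1.8025² / 0.04 = 81.2, so 82 per group for a fixed design. With one Lan-DeMets O'Brien-Fleming look at half information and the stated futility rule, simulated power is 79.9% at 82 per group and 80.8% at 84. The stated 84 reproduces.

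**2. Mechanism by hand.** Assume a null rate of 40%, balance on risk-factor count essentially perfect, and no centre effect. The relative overstatement of the SE is 1/√(1 − R²), where R² is the share of outcome variance explained by the count.

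- Assumed odds ratio (OR) 4 for three versus two factors, 30% with three. The rate with two is 0.30 (odds 0.4286). The rate with three is 1.714/2.714 = 0.632. Check: 0.7·0.30 + 0.3·0.632 = 0.40. R² = 0.3·0.7·(0.632 − 0.300)²/0.24 = 0.0231/0.24 = 0.096. The ratio is 1/√0.904 = 1.052.
- Assumed OR 2, 20% with three. The rates are 0.366 and 0.536. R² = 0.2·0.8·0.170²/0.24 = 0.019. The ratio is 1.010.

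So the count alone overstates the SE by roughly 1% to 5%.

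**3. Simulation of the stated allocation.** 168 patients, ten centres of assumed unequal size, 80/20 minimisation, single look at two-sided 5%, 5,000 trials per row. Monte Carlo error is about 0.3 point on type I error and 0.5 point on power. The odds ratio, the centre SD (logit scale) and the share with three factors (20-40%) are assumptions, because the document gives none of them.

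| OR, 3 vs 2 / centre SD | Mean pooled SE vs true SD, null | Type I error, Z | Power, Z | Power, Mantel-Haenszel (MH) on count | Power, linear model on count + centre |
|---|---|---|---|---|---|
| 1 / 0 | 0.0754 vs 0.0755 | 5.3% | 82.1% | 82.0% | 81.8% |
| 2 / 0.3 | 0.0753 vs 0.0742 | 4.7% | 82.8% | 82.9% | 83.2% |
| 3 / 0.5 | 0.0752 vs 0.0726 | 4.2% | 83.0% | 83.9% | 84.7% |
| 4 / 0.7 | 0.0751 vs 0.0714 | 4.2% | 83.6% | 85.0% | 86.4% |
| 5 / 1.0 | 0.0749 vs 0.0674 | 3.4% | 83.9% | 86.4% | 88.7% |

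The SE ratios for the last four rows are 1.015, 1.036, 1.052 and 1.111. With no centre effect, the Z test ran at 5.0% (OR 2) and 5.1% (OR 3), so no conservatism was visible beyond Monte Carlo error.

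Separate runs agree:

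- At OR 2.5-4 and centre SD 0.3-0.5, the Z test rejected in 4.0-4.5% of null trials against 4.9%. Adjusting for count and centre raised power from 82.0% to 83.6% and from 83.4% to 86.3%.
- At OR 4 and SD 0.5, null rejection was 3.6%, and MH on count raised power from 83.0% to 85.5%.

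**4. Which adjustment holds its error.**

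- MH on count ran at 5.2%, 4.9%, 4.4%, 4.7% and 3.9% down the table (nominal 5%).
- The linear model on count plus centre ran at 4.9-5.6%, so part of its apparent gain may come from a slightly high error rate.
- Logistic standardisation with robust variance on count plus centre exceeded 4.9%: 5.2-6.0% at 168 patients, and 6.0-7.1% at the 84-patient interim with 6-12% of fits failing.
- Stratifying on all 20 centre-by-count cells lost power when prognosis was weak: 79.3% vs 82.1% (OR 1) and 80.7% vs 82.8% (OR 2).

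**The case against.** The strongest reply is that nothing is broken. The trial is sized on the very test it will use, that test kept 82-84% power in every scenario against a planned 80%, and its error is on the safe side. All of this stands. A reader might infer that the primary test loses error control or that the trial is underpowered, and the document supports neither.

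The size is also assumed. Every patient has at least two factors, so the contrast that matters is three versus two, and no figure is given for it. A reader might take the 20-fold risk in Conditions for patient selection as that figure. It describes patients over 55 with a BMI above 30, who already have two factors, and it states no comparator. Nothing in the document supports a centre effect. This is why the point is conditional.

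A reader might add that the confidence interval is too wide. The primary analysis section specifies no interval for the treatment difference, so that has no footing here.

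Finally, an adjusted analysis could be left to the SAP, which is still to be written. That would do for a supportive analysis. It does not cover the primary test, which this document already fixes down to its variance estimator and p-value limits.

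**Conclusion.** The mismatch between allocation and analysis is real and its consequence is modest. If the balancing factors are prognostic, the pooled SE is somewhat too large and the Z test is conservative. At odds ratios of 2-4 and centre SD 0.3-0.5, type I error is about 3.5-5% against 4.9%, and roughly 0.5-3 points of power are forgone. The lower end is within simulation noise, and with no prognostic value the loss is zero. Only the more extreme assumption (OR 5, SD 1.0) reaches about 5 points (88.7% vs 83.9%).

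The direction is secure. The size rests on assumed prognostic strength, centre sizes and share with three factors, and on a single look at 168 evaluable patients. This is a worthwhile, low-cost efficiency improvement and not a validity defect.

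**What to change.** Before any unblinded look, redefine the primary comparison as a Mantel-Haenszel risk difference and test stratified by number of risk factors (two versus three), judged at the plan's group-sequential boundaries. With stratum weights w = n1·n0/n, the estimate is Σw·(p1 − p0)/Σw, so the effect measure remains a difference in proportions. Keep the unadjusted pooled Z test as a sensitivity analysis.

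Add centre only in a parsimonious form, for example with small centres pooled, and only if simulation of the actual minimisation shows error control at both 84 and 168 patients. Run the count-stratified test through the same simulation. Do not use logistic standardisation with uncorrected robust variance on count plus centre, or a 20-cell stratification.

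The cost is a protocol and SAP wording change plus a little more analysis work. Both variables are already in the randomisation system, and seven patients had been enrolled when the article was submitted. Stratifying on count alone recovers only part of the loss if centres also differ (for example 83.9% against 84.7% at OR 3, SD 0.5), and gains nothing if the count is not prognostic.

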#### Secondary outcome, exploratory, and sensitivity analyses

Selected efficacy analyses will be repeated in the per protocol population (i.e., subset of the ITT population meeting the following criteria: all eligibility criteria fulfilled, at least one dose of allocated treatment administered). The safety population will be used for reporting the safety and treatment exposure data. A modified ITT population will be used for HRQoL analysis, considering all randomized patients with at least the baseline HRQoL questionnaire available. Continuous variables will be summarized using descriptive statistics, i.e., the number of patients with available data (n), mean, median, standard deviation (SD), 25–75% quartile (Q1–Q3), minimum, and maximum. Continuous variables could be transformed to categorical variables using the median or using conventional cut-offs from bibliography or clinical practice. Frequencies in tables will be presented by arm, total frequency, percentages, and missing modality. Qualitative variables will be summarized by means of counts and percentages. Unless otherwise stated, the calculation of proportions will be based on the sample size of the population of interest. The rate of incidence of NODAT will be determined using confidence interval (CI) and compared using Chi 2 test. Univariate and multivariate logistic analyses will be done to identify the independent prognostic factor of the rate of incidence of NODAT and to compute the odds ratio with 95% CI. The continuous variables will be treated as quantitative and qualitative data using cut-offs in anticipation of elaborating a practical clinical tool. Factors will be considered for inclusion in the model if the univariate p value is ≤ 0.1. Interactions between treatment and some variables will be tested at a two-sided 10% level (i.e., a p value > 0.1 indicates no evidence of heterogeneity of treatment effect across the subgroups for each factor). All tests will be performed in an exploratory purpose at a two-sided 5% significance level.

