### Study outcomes

The primary endpoint is the proportion of diabetic patients 1 year after transplantation, defined as one of the following criteria: patients receiving a diabetic treatment, patients have a fasting glucose above 7 mmol/l, and/or patients with an abnormal oral glucose tolerance test (OGTT).

The criteria for secondary assessments are: glycated hemoglobin (HbA1c) 3 months, 6 months, and 12 months after transplantation; occurrences of acute rejection, infection, graft loss, and patient death 3, 6, and 12 months after transplantation; clinical history (cardiovascular history, baseline renal disease, dialysis, anti-human leukocyte antigen antibodies, dyslipidemia, hypertension, type of donor, duration of ischemia, cytomegalovirus (CMV) status, CMV prophylaxis, pneumocystis prophylaxis); biological data (creatinine, uric acid, C reactive protein (CRP), blood sugar balance, lipid profile, liver function tests, pancreatic balance, and blood counts); health-related quality of life (HRQoL; Renal Transplant Quality of Life (ReTransQoL) questionnaire), 8 days and 3, 6, and 12 months after transplantation; and the cost-effectiveness of prevention of diabetes with vildagliptin correlated to outcomes.

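### The exploratory NODAT prognostic model selects factors by univariate p ≤ 0.1 on about 50 to 67 events, a rule prone to false independent factors and optimistic discrimination (minor)

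*Protocol article*

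**What the plan says.** The section on secondary, exploratory and sensitivity analyses states: "Univariate and multivariate logistic analyses will be done to identify the independent prognostic factor of the rate of incidence of NODAT", with odds ratios and 95% confidence intervals. A factor may be taken into the multivariable model when its univariate p value is 0.1 or below. Continuous variables are to be used both as measured and cut, "in anticipation of elaborating a practical clinical tool". The section ends by describing all its tests as exploratory, two-sided, at 5%.

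The section does not list the factors to be tested. Study outcomes names 11 clinical-history items, among them "type of donor, duration of ischemia, cytomegalovirus (CMV) status, CMV prophylaxis, pneumocystis prophylaxis", and 8 biological items, as secondary assessments. Under Conditions for patient selection, the Discussion keeps age, BMI and family history as enrolment risk factors. The justification of the primary outcome says diabetes results will be correlated with medical history and biology.

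The number of events follows from the sample size section: "The estimated proportion of diabetic patients 1 year after transplantation is 40% in group 2", a halving to 20% is expected with vildagliptin, and 84 patients per group are needed. On losses it adds: "We expect 10% of patients at 1 year to be non-evaluable and thus we will include 186 patients in total".

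**The concern.** A univariate p-value screen followed by a joint fit on the same patients uses the data twice. A noise factor that passes the screen does so because its association in this sample is large by chance, and the joint model then reports that inflated odds ratio. Too many factors get called independent, and the model separates cases from non-cases better here than it will elsewhere. The problem grows as events per candidate fall.

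The primary comparison is not at stake. What is at stake is the published list of independent NODAT factors and any bedside tool that starts from it. The concern attaches to a selection rule the article fixes, so an analysis plan written in line with the article would inherit it.

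**Working it through.** **1. The plan's sample size.** Inputs: 40% v 20%, pooled Z test, two-sided 5%, power 80%. With a mean rate of 0.30:

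n per arm = [1.96 × √(2 × 0.30 × 0.70) + 0.8416 × √(0.40 × 0.60 + 0.20 × 0.80)]² / 0.20² = (1.270 + 0.532)² / 0.04 ≈ 81.2, so 82.

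The stated 84 fits this with a small inflation for one interim look. 168 / 0.90 = 186.7, against 186 stated. The base of 168 evaluable patients is sound.

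**2. Events for the logistic model.**
- Design rates: 84 × 0.40 + 84 × 0.20 = 33.6 + 16.8 = 50.4, which is 30% of 168.
- No treatment effect: 168 × 0.40 = 67.2.
- The 63 events printed in the sample size section belong to the supportive time-to-event analysis. They fall between these two values.

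**3. Candidates (assumption).** If all named items were eligible: 11 history + 8 biological + 3 enrolment factors + treatment = 23. Events per candidate: 50.4 / 23 = 2.2, or 67.2 / 23 = 2.9. The true list could be longer, since lipids, liver tests and blood counts are panels, or shorter if the analysis plan restricts it. With 10 candidates the figures are 5.0 and 6.7.

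**4. Hand check of false selection, independent noise factors.** Of 22 noise factors, 22 × 0.1 = 2.2 are expected to pass the screen, and at least one passes with probability 1 − 0.90²² = 0.90. The chance that at least one reaches 5% is roughly 1 − 0.95¹⁰ = 0.40 for 10 factors and 1 − 0.95²³ = 0.69 for 23.

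**5. Simulation of the stated rule.** 168 patients, 30% events, half the candidates binary and half continuous, all noise. Screen at p ≤ 0.1, fit the survivors jointly, call a factor independent at p < 0.05. 1,000 trials per row:

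| Noise candidates | Correlation | Mean entering | At least one false independent factor | Mean apparent AUC (truth 0.50) |
|---|---|---|---|---|
| 23 | 0 | 2.3 | 66% | 0.64 |
| 23 | 0.3 | 2.2 | 41% | 0.61 |
| 15 | 0 | 1.4 | 51% | 0.60 |
| 10 | 0 | 1.0 | 38% | 0.57 |
| 10 | 0.3 | 1.0 | 26% | 0.57 |

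The Monte Carlo standard error is about 1.5 percentage points (√(0.66 × 0.34 / 1000) = 0.015). Repeat runs gave 25% to 68% over the same settings.

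**6. A setting closer to the plan.** Treatment works as designed (40% v 20%) and is forced in, with noise factors screened alongside it; 800 trials per row. AUC is averaged over trials in which at least one noise factor entered.

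| Noise candidates | Correlation | At least one false independent factor | Apparent AUC | AUC in new data |
|---|---|---|---|---|
| 22 | 0 | 64% | 0.70 | 0.59 |
| 22 | 0.3 | 37% | 0.69 | 0.59 |
| 10 | 0 | 38% | 0.68 | 0.60 |
| 10 | 0.3 | 27% | 0.68 | 0.60 |

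For comparison, treatment alone has a true AUC of 0.5 + (33.6/50.4 − 50.4/117.6) / 2 = 0.5 + (0.667 − 0.429) / 2 = 0.62. The selected noise makes the model look better here and predict slightly worse elsewhere.

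**The case against.** Four arguments weigh against the point, and each has some force.

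- **The candidate count.** A reader might infer that the model screens at least 23 factors. The article does not say so: the history and laboratory items are listed as secondary assessments, and no section makes them model covariates. The figure of 23 is only a plausible upper scenario, so the results above are given from 10 candidates upwards.
- **Missing safeguards.** A reader might infer that there will be no internal validation or shrinkage. The article is condensed and defers to an analysis plan to be approved before the database is frozen. Silence on validation is therefore not a fault. The screening rule itself is stated, and that part stands.
- **Treatment.** A reader might infer that randomised treatment could be dropped from the model. The entry sentence concerns prognostic factors, says only that they may be considered, and does not say how treatment is handled. Forcing treatment in is worth writing down, but its absence here shows nothing.
- **The exploratory label and the noise scenario.** All these tests are labelled exploratory, and the primary Z test does not depend on them. The all-noise scenario is also pessimistic: the plan expects a treatment effect and treats age, BMI and family history as real predictors. Even so, the second simulation, with a real treatment effect, shows AUC falling by 0.08 to 0.11 in new data. The label excuses the lack of multiplicity control; it does not remove bias from selected odds ratios.

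**Conclusion.** The point holds as a minor one. The article fixes a weak selection method for a model with about 50 to 67 events, and gives that model an aim, independent factors leading towards a tool, that the method serves poorly. With 10 to 23 noise candidates and correlation of 0 to 0.3, the chance of at least one false independent factor is about 25% to 68%, and apparent AUC is about 0.57 to 0.64 against a truth of 0.50.

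These sizes rest on an assumed candidate count, on all screened factors being noise, and on every factor that passes the screen being entered. To say that false factors are likely would go too far: the chance exceeds one half only with many nearly uncorrelated candidates, and is 26% to 41% in the settings with correlation 0.3. The text also only anticipates a tool; it does not commit the trial to releasing one unvalidated. The primary analysis is unaffected.

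**What to change.** In the analysis plan, replace the univariate p ≤ 0.1 selection by one of two methods:

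- a short pre-specified set of about five parameters known at D0, for example treatment, age, BMI, family history and one D0 laboratory value, all retained whatever their p values, with randomised treatment forced in. This gives 50.4 / 5 ≈ 10 events per parameter. Ten per parameter is a common guide and an assumption here, not a figure from the article; or
- penalised logistic regression on the full list, with the list written down beforehand.

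With either method, report bootstrap optimism-corrected AUC and calibration, describe all other factors univariately only, and present any tool as hypothesis-generating until externally validated.

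The cost is a paragraph of wording and a bootstrap run. At submission the article had the plan still to be approved and seven patients enrolled, so nothing in the conduct of the trial changes. The downside is that fewer factors will be reported as independent.
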